### Trial monitoring

The trial is considered low risk without stopping rules, so Investigational Medicinal Products will not be used. The independent Trial Oversight Committee (TOC) will review the protocol and the statistical analysis plan, and review recruitment of patients, compliance with protocol, adverse events or effects, and the collection of complete data. The research staff are independent experts specializing in clinical trials, cancer nursing, or statistics. The Trial Management Committee will supervise the trial procedures and progress, and the outcomes will be reported regularly.

### Protocol amendments

The sponsor is responsible for submitting materials to the local ethics committee. During this process, the principal investigator may be trained in any program modification. If necessary, any retraining shall be provided.

### Sample size

The sample size was estimated in this study by using perceptive cognitive impairment as the main effect indicator, which refers to the results of Oh et al. [26]. Using the G*Power 3.1 software, 58 cases of the total sample can be calculated with a test power of 0.80. Considering the 20% dropout rate, the total sample size for this study is about 70 patients randomized to the intervention group or the control group.

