**Method:**

A single-blinded, randomized control trial was designed. The trial will recruit 70 patients with early-stage breast cancer scheduled to receive chemotherapy from Shanghai in China. All participants will be randomly assigned to (1:1) the supervised Baduanjin group (5 times/week, 30 min each time) or the wait-list control group for 3 months. The effect of Baduanjin exercise intervention will be evaluated by outcome measures including subjective and objective cognitive function, symptoms (fatigue, depression, and anxiety), and health-related quality of life at pre-intervention (T0), 8 weeks (T1), and 12 weeks (T2). The PCI score in the FACT-Cog as the primary cognitive outcome will be reported descriptively, while effect sizes and 95% confidence intervals (CIs) will be calculated. The collected data will be analyzed by using an intention-to-treat principle and linear mixed-effects modeling.

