### Randomization and blinding

Participants will be randomly assigned to 1 of 2 groups—an intervention group or a control group—in a 1:1 ratio using the SPSS 24.0 software. The allocation of the result will be put into sealed, opaque envelopes by a study administrator not involved in the study, and the group numbers will be subsequently disclosed. Given that Baduanjin exercise is a well-known exercise to the study population, blind method is conducted to assessors only, not physicians or patients. In addition, all participants will be asked not to discuss the practice with each other to minimize bias. The assessor will also be instructed not to acquire the participant’s exercise information. Participants are allowed to withdraw without giving a reason at any time. If any patient experiences adverse effect during exercise, such as palpitation or severe upper limb lymphedema, but still wishes to participate, there will be a therapist available who will evaluate whether the patient can continue on the study.

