### Data collection

All the data will be collected from participants, including those who discontinue the intervention. Most of the outcome data will be collected via the provided paper-and-pencil measures (anonymised by participant ID). If participants are interested in electronic measures (anonymised by participant ID), these will be provided.

The cognitive assessors will conduct a comprehensive training in scoring the measures. Interrater reliability will be determined, and discrepancies will be resolved by consensus. After participants have been randomized, dropout and premature termination from the two groups at any point will be recorded along with relevant reason. Participants can choose to withdraw and will not be affected at any time while declining to participate or withdrawing from the trial. In some cases, participants will discontinue the intervention, such as illness, progression of their disease, or inability to engage despite adjustment of the program. Participants who are withdrawn from the intervention during the trial will not continue to follow-up but will not be replaced.

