### Data analysis

Demographics and other characteristics will be reported descriptively to summarize the distribution of all variables via the statistics software (SPSS 24.0). The means and SD will be calculated for continuous normally distributed variables and medians and ranges for non-normally distributed variables. Categorical variables will be presented by absolute numbers and percentages. All cases for both baseline and follow-up measurements will be analyzed for the different outcomes. If missing values exceed 10%, we will impute missing values on covariates by using multiple imputation.

According to the intention-to-treat principle, we will compare the number of patients showing post-intervention 7-point improvement in the PCI scores between the intervention group and the control group using Fisher’s exact tests. A linear mixed-effect model for repeated-measures analysis will be used to analyze the changes in cognition such as treatment, time point, and the interaction between treatment and time point. The between-group effect size will be calculated in post-treatment means (dividing the between-group difference with the pooled standard deviation). The effect sizes of 0.20, 0.50, 0.80, and 1.30 represent small, medium, large, and very large effect, respectively [41]. Two-sided significance level for all tests is 0.05.

Linear regression analysis adjusted for baseline will be used to assess the association between changes in cancer-related symptoms (fatigue, anxiety, and depression) and changes in cognitive function. Adherence to the Baduanjin exercise will be noted by adherence rate ((total frequency − absenteeism)/total frequency × 100%).

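### Minor arithmetic error: the 20% dropout allowance was added to 58 rather than divided out, so 70 randomized covers only about 17% dropout

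*Protocol article*

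**What the plan says.** The Sample size section of the protocol article gives the evaluable total and its power: "58 cases of the total sample can be calculated with a test power of 0.80". It then allows for loss: "Considering the 20% dropout rate, the total sample size for this study is about 70 patients". The Abstract (Method) repeats the target without the word of approximation: "The trial will recruit 70 patients with early-stage breast cancer scheduled to receive chemotherapy". Allocation is equal, "in a 1:1 ratio using the SPSS 24.0 software" (Randomization and blinding).

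The effect size behind the 58 is not given as a number. The section only points to the results of an earlier study, cited in the Background as a trial of medical Qigong. The test and the significance level are not stated there either, but Data analysis sets the level: "Two-sided significance level for all tests is 0.05".

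On patients who leave the intervention, Data collection says: "Participants who are withdrawn from the intervention during the trial will not continue to follow-up but will not be replaced".

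**The concern.** Three figures stand side by side in one section: 58 needed, 20% lost, about 70 randomized. If a fifth of 70 patients are lost, fewer than 58 are left, so the dropout allowance does not do what the section says it does. The section is the trial's public justification for its size, and 58 is the bare requirement with no margin shown. A reader would take it that power 0.80 is protected against 20% loss. At stake is the accuracy of that statement and, to a small degree, the power itself.

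**Working it through.** **Inputs.** Evaluable total 58, power 0.80, dropout 20%, randomized total about 70 (all from Sample size; the Abstract also gives 70); 1:1 allocation (Randomization and blinding); two-sided 0.05 (Data analysis).

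**1. Reproducing the plan's figure.** Multiplying by one plus the dropout rate: 58 × 1.20 = 69.6, which rounds to 70. This matches the stated number.

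**2. The allowance that keeps 58.** If N are randomized and a fraction 0.20 is lost, N × (1 - 0.20) must be at least 58:
- N = 58/0.80 = 72.5, so 73 in total.
- With equal arms, 29/0.80 = 36.25, so 37 per arm and 74 in total.
- Check: 72 × 0.80 = 57.6 (too few); 73 × 0.80 = 58.4 (enough).

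The stated 70 is therefore 3 below the required total, or 4 below it with equal arms.

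**3. What 70 delivers.**
- At 20% dropout: 70 × 0.80 = 56 evaluable, 28 per arm, which is 58 - 56 = 2 short.
- Largest dropout that still leaves 58: 1 - 58/70 = 0.171, about 17%.

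Steps 1 to 3 use only stated figures and do not depend on the missing effect size.

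**4. Effect on power (assumption needed).** Assume a two-sample t-test at two-sided 0.05 with n per arm, 2n - 2 degrees of freedom and noncentrality d × √(n/2).
- Suppose power at 29 per arm is exactly 0.80. Solving for the standardized difference gives d ≈ 0.749. With that d, power at 28 per arm is 0.7856.
- The normal approximation agrees: d = (1.960 + 0.842) × √(2/29) ≈ 0.736, and power at 28 per arm is 0.7861.
- A sample-size program returns the smallest number that reaches the target, so power at 58 may be a little above 0.80. If 58 is the smallest even total that reaches 0.80, then power at 56 is below 0.80 by definition, and it is no lower than the 0.7856 just found.

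The range for power at 56 is therefore about 0.786 to just under 0.80, a deficit of at most about 1.4 percentage points (0.80 - 0.786 = 0.014).

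**The case against.** **The target is approximate.** The section says about 70, and a planned dropout rate is only a guess. Both points bear on importance. Neither removes the error: 73 or 74 is not about 70 in this context, the stated number is the rounded 69.6, and the Abstract gives 70 outright.

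**Dropout might be meant as a percentage of completers.** On that reading 58 × 1.20 would be right. It is not the ordinary meaning, and Data collection records dropout from the point of randomization, so the base is those randomized.

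**Patients who drop out are not wholly lost to the analysis.** Data analysis names the intention-to-treat principle and a linear mixed model, and assessments fall at baseline, 8 weeks and 12 weeks. A patient lost after week 8 still contributes the week 8 value. Data collection also says that data will be gathered from those who stop the intervention. This softens the consequence, and that much stands. It does not repair the figure: the same section ends follow-up for withdrawn participants and does not replace them, and the plan's own allowance treats dropouts as lost.

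**The trial is described as a pilot.** The Abstract says that the primary score will be reported descriptively with effect sizes and confidence intervals. Data analysis nevertheless plans tests at 0.05, so power is not irrelevant, but a deficit of this size matters little in such a study.

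**Stronger readings that the documents do not support.** A reader might infer that the trial is materially underpowered, that its power is 78.6%, or that it must enrol 3 or 4 more patients. The shortfall is 2 evaluable patients. The 78.6% is the lower end of a range that rests on an assumed test and a back-solved effect, and it is not a figure from the protocol. Rewording the tolerated dropout is enough to make the section correct.

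**Conclusion.** The point holds as a minor arithmetic error. The stated 58, 20% and 70 do not agree with one another: 70 at 20% dropout leaves 56, and 70 protects 58 only up to about 17% dropout. This part rests on the document's figures alone, with dropout taken as a share of those randomized.

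The loss of power is at most about 1.4 percentage points, and that size is conditional on the two-sample t-test assumption set out in the working. Whether 58 is itself the right number cannot be checked from the article, and nothing here turns on it. No design feature, planned analysis or likely conclusion changes.

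**What to change.** Reword the Sample size section so that the figures agree. For example: 70 randomized patients keep 58 evaluable, the number calculated for power 0.80, if dropout is at most about 17%; at 20% dropout 56 remain and power falls slightly below 0.80. If a number for power is wanted, the sponsor should compute it from the effect size and test actually entered in the software. The range of about 0.786 to just under 0.80 should be used only with its assumptions stated. It may be added that keeping 58 at 20% dropout would have needed 73, or 74 with equal arms.

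The cost is one or two sentences and a slightly less favourable dropout statement. Recruitment began on 1 June 2020 (Trial status), and this correction leaves the target of 70 in the Abstract unchanged, with no extra enrolment.

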### Data collection

All the data will be collected from participants, including those who discontinue the intervention. Most of the outcome data will be collected via the provided paper-and-pencil measures (anonymised by participant ID). If participants are interested in electronic measures (anonymised by participant ID), these will be provided.

The cognitive assessors will conduct a comprehensive training in scoring the measures. Interrater reliability will be determined, and discrepancies will be resolved by consensus. After participants have been randomized, dropout and premature termination from the two groups at any point will be recorded along with relevant reason. Participants can choose to withdraw and will not be affected at any time while declining to participate or withdrawing from the trial. In some cases, participants will discontinue the intervention, such as illness, progression of their disease, or inability to engage despite adjustment of the program. Participants who are withdrawn from the intervention during the trial will not continue to follow-up but will not be replaced.

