### Baduanjin exercise group

Baduanjin exercise is conducted according to the standards promulgated by the General Administration of Sport in China in 2003, which consists of 10 postures (including the beginning and ending posture). A professionally trained Qigong specialist will uniformly train subject researchers to learn Baduanjin. Researchers will then conduct on-site instruction to guide patients and correct their movements. Participants will also be provided with video demonstration. Before the first cycle of chemotherapy, the patients will conduct the first session in the hospital, then follow the video workout at home. Recommended training time is 5 times a week, for half an hour each time, during the 12-week study period. The program begins with stretching the joints, inhalation and exhalation for 2 min respectively, and two 12-min Baduanjin sessions, followed by 2 min of muscle relaxation exercises. Patients’ log will be recorded including any obstacles during exercise at home. When the patients go to the hospital to receive chemotherapy, the feedback of exercise log will be collected and checked. To promote participant retention, we will follow up and encourage the patients through WeChat twice weekly, asking the factors that hinder their activities and solving it in time. In addition, small gifts will be given to patients (e.g., towels and toothbrushes) to promote their exercise enthusiasm at each assessment.

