### Wait-list control group

Patients randomized to the control group are given a face-to-face health education according to the handbook to maintain their usual healthy lifestyle. Disease-related questions raised by the patients will be directly communicated or answered through WeChat online. Meanwhile, researchers need to ask patients about their conditions twice a week. Patients can exercise the affected limb through exercises including abduction, forward flexion, backward extension, internal rotation, and wall climbing, according to the guideline and standard for the diagnosis and treatment of breast cancer set forth by the Chinese Anti-Cancer Association (2019 edition), and the patients are not asked to conduct other aerobic activities. The supervised Baduanjin exercise for participants will be offered if they wish after the completion of study.

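### The protocol both continues and ends follow-up for patients who stop the intervention; ending it undermines the intention-to-treat comparison and may bias it in either direction

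*Protocol article*

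**What the plan says.** Three statements in the protocol article bear on this point.

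- **Data collection, opening sentence:** "All the data will be collected from participants, including those who discontinue the intervention".
- **Data collection, closing sentence:** "Participants who are withdrawn from the intervention during the trial will not continue to follow-up but will not be replaced". The sentence just before it explains that in some cases "participants will discontinue the intervention, such as illness, progression of their disease, or inability to engage despite adjustment of the program".
- **Data analysis:** "According to the intention-to-treat principle, we will compare the number of patients showing post-intervention 7-point improvement in the PCI scores", using Fisher's exact test. In addition, "A linear mixed-effect model for repeated-measures analysis will be used to analyze the changes in cognition". On missing data, the section says "If missing values exceed 10%, we will impute missing values on covariates by using multiple imputation".

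The Wait-list control group section describes no exercise programme during the trial beyond guideline exercises for the affected limb: "Patients randomized to the control group are given a face-to-face health education according to the handbook to maintain their usual healthy lifestyle". Data collection also provides for recording early departures, with reasons, in both groups.

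**The concern.** A site that follows the opening sentence will keep measuring a patient who has stopped exercising. A site that follows the closing sentence will not. The number of T1 and T2 outcomes collected, and from whom, then depends on which sentence staff act on.

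If the closing sentence prevails, the protocol itself creates missing outcomes, triggered by an event after randomization. An intention-to-treat comparison needs the outcome of each randomized patient whether or not she kept exercising. The trigger is also unlikely to be neutral. Illness, progression and failure to cope with the programme plausibly go with worse cognition, and a programme to be removed from exists mainly in one arm. The comparison at stake is the primary one, on the FACT-Cog PCI score. Outcomes that were never collected cannot be recovered at analysis.

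**Working it through.** **1. Do the two sentences concern the same patients?** The opening sentence covers those who discontinue the intervention. The closing sentence covers those withdrawn from the intervention, and directly follows the list of reasons for discontinuing it. Voluntary withdrawal from the trial is handled separately, earlier in the same section. The natural reading is one group of patients under two opposite rules.

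**2. Does the analysis section make up for the loss?** The imputation rule is limited to covariates. No stated rule says how a missing PCI score enters the Fisher test. The mixed model uses whatever scores exist: T0 and T1 for a patient lost after 8 weeks, T0 only for one lost earlier.

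**3. Inputs for an illustration.** The documents give no figure for this bias, so there is none to reproduce.

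- From the protocol: about 70 patients randomized 1:1, so 35 per arm; a 7-point PCI threshold; and a 20% dropout allowance for the whole trial, not split by arm (58 × 1.20 = 69.6, about 70).
- Assumed: that 20% of the exercise arm (0.20 × 35 = 7 patients) is lost through this rule and no controls are; the PCI gap g between retained and lost patients; and, for the simulation, an SD of change of 12 and a correlation ρ between poor outcome and withdrawal.

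**4. Mean difference among completers.** Let w be the share of the exercise arm lost. The full-arm mean is (1 − w) × retained mean + w × lost mean. The retained mean therefore exceeds it by w × g.

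- g = 5: 0.20 × 5 = 1.0 point, and 1.0/7 = 14% of the threshold.
- g = 10: 0.20 × 10 = 2.0 points, and 2.0/7 = 29%.
- g = 0: no bias.
- g = −4 (lost patients would have done better): 0.20 × (−4) = −0.8.
- If controls are lost too, the net bias is w × g in the exercise arm minus the same product in the control arm. It is zero when the two are equal.

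**5. Responder comparison with missing counted as non-response.** With no true effect and SD 12, the chance of a gain of at least 7 points is P(Z > 7/12) = 0.28. If withdrawal is unrelated to outcome, losing 20% of the exercise arm removes 0.20 × 0.28 = 0.056 from its response rate. That is −5.6 percentage points, against Baduanjin.

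**6. Simulation.** 35 per arm, no true effect, 20% lost from the exercise arm only, 3,000 trials per row. Positive values favour Baduanjin.

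| ρ | Mean difference, completers (points) | Two-sided rejection, t-test | Responder difference, completers (pp) | Responder difference, missing = non-response (pp) |
|---|---|---|---|---|
| 0 | about 0 | 5.3% | −0.1 | −5.6 |
| 0.3 | +1.2 | 6.5% | +2.9 | −3.3 |
| 0.5 | +2.0 | 10.2% | +4.9 | −1.7 |
| 0.8 | +3.2 | 20.2% | +6.6 | −0.4 |
| −0.3 | −1.3 | 7.0% | −3.8 | −8.7 |

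With 20% lost from both arms by the same mechanism, the mean bias is about zero in every row. With a true 7-point effect, ρ = 0.3 and loss from the exercise arm only, the true responder difference of 22 percentage points becomes 26 among completers and 15 if missing counts as non-response. The mixed model was not simulated.

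**The case against.** **The sentences might be reconciled.** A patient who chooses to stop exercising could still be measured, while one removed by staff is not. The Randomization and blinding section gives this some support: after an adverse effect during exercise, a therapist judges whether the patient may go on in the study. The reading is weak, because the reasons listed immediately before the closing sentence are reasons for discontinuing. Even if accepted, it leaves patients removed by staff without outcomes, so the conflict with intention-to-treat remains.

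**A reader might infer that the rule biases the trial towards Baduanjin.** The documents do not establish this. They give no loss by arm, no outcome gap, and no rule for a missing score in the Fisher test. The sign reverses when missing counts as non-response. A likelihood-based mixed model may also remove part of the bias if T0 and T1 scores explain the loss. This objection stands.

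**A reader might infer that only the exercise arm loses patients.** Data collection expects departures from both groups, and controls can fall ill, progress or withdraw. What stands is that the rule can act asymmetrically.

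**A reader might also infer unequal retention from the gifts.** The exercise section says "small gifts will be given to patients (e.g., towels and toothbrushes) to promote their exercise enthusiasm at each assessment", and the control section mentions none. Silence in a condensed article does not show that controls receive none, and both arms have twice-weekly contact. This is not part of the finding.

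**Conclusion.** The concern holds as an internal contradiction with a consequence for the primary comparison. The contradiction needs no assumption. Nor does the conflict with intention-to-treat: ending follow-up when a patient leaves the intervention discards outcomes that the analysis needs, and no stated rule replaces them.

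Bias is possible but its direction is open. It plausibly favours Baduanjin if sicker patients are lost mainly from that arm and available cases are analysed. It goes against Baduanjin if missing counts as non-response. It is about zero for the mean difference if losses are balanced or unrelated to outcome.

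The 1.0 to 2.0 points are not an estimate for this trial. They assign the whole 20% allowance, which covers all causes and both arms, to this one rule in one arm, and they assume the gap. They show only that the effect could be appreciable against a 7-point threshold.

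**What to change.** In Data collection, delete the closing no-follow-up sentence and keep the opening one. State that stopping the exercise is not withdrawal from the study. Collect the T1 and T2 FACT-Cog and cognitive tests from all randomized participants unless they withdraw consent for data collection. Record discontinuation of the intervention separately from withdrawal from the study, by arm and with reasons. This changes data collection only and leaves the clinical grounds for stopping the exercise as they are. With full follow-up, w = 0 for this cause and the bias term w × g vanishes whatever g is.

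The Trial status section expected completion by 1 June 2021 and the article is dated 19 June 2021, so some assessments may already have been missed under the rule. If so, report those losses by arm and reason and add a sensitivity analysis for missing outcomes.

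The cost is a one-sentence amendment and a few extra assessments by the existing assessors, at most two per affected patient (in the illustration, 7 × 2 = 14). The protocol already offers electronic measures, which would ease collection of the questionnaires.
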